### Sample size

No studies are currently available that directly compare rehabilitation of chewing function with a control condition on neurocognitive measures. We, therefore, designed our RCT as a superiority trial with enough statistical power to detect a difference in outcome between treatments (if present) with a medium effect size (partial eta square, eta2). For the longitudinal analysis that assesses rehabilitation differences, we expect an effect size (partial eta square, eta^2^) on the NA of at least 0.06. With α set to 0.05 and power at 0.80, a sample of 30 participants in each group is required. The power calculation of the repeated measures analysis is estimated with within-participant factors, which also controls for the between-participant variance. However, due to the moderate rate of dropouts (20–25%) observed across different ongoing studies, optional non-participation of MRI screening, and technical difficulties (e.g., movement artifacts) during brain imaging, we estimate that inclusion of 40 participants in each group is required to meet the demands for statistical power. However, only the first 20 participants willing and eligible to participate in the MRI procedures in each group will undergo brain imaging due to practical and logistical reasons. The MRI acquisitions are optional since there are more contraindications medically and patients are more reluctant to participate. By making MRI optional participants can still be included in the study when MRI acquisitions are not feasible.

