*Neuropsychological assessments* The NA are approximated to 90 min per test occasion and are conducted prior to the protocol by a research assistant blinded to the randomization. The neuropsychological assessments are state-of-the-art tests with good psychometric validity translated into Swedish. The aim is to use the cognitive tests that are sensitive to change and measure a broad range of cognitive domains.

The assessed cognitive domains and specific tests are:

*Episodic memory* The Ray Auditory Verbal Learning Test (RAVLT) [46], the BVMT-R [43].

*Executive functions* The Trail Making Test (TMT) trial 4 from Delis-Kaplan Executive Function System (D-KEFS) [47], the Verbal Fluency (VF) test from D-KEFS, and the Color-Word Interference Test from D-KEFS.

*Attention/working-memory* The Digit Span from Wechsler Adult Intelligence Scale (WAIS) 4th edition[48], the Digit Symbol from WAIS-IV, and the Trail Making Test (TMT) trial 1–3, and 5 from D-KEFS.

*Visuospatial functions* The Block Design from WAIS-IV.

*Logical thinking* The Matrix Reasoning from WAIS-IV.

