### Statistical methods

The data from the study will be entered in a Microsoft Excel sheet and exported to statistical software packages like SPSS Inc, Statistica, StatSoft Inc, or similar advanced analytics software packages for analysis. The result from the cognitive testing will be analyzed as repeated measure Analysis of covariance (ANCOVAs) with groups (experimental and control) and time (pre-and post-rehabilitation) as factors. Group-by-time interaction, the main effect of the group, and the main effect of time will be evaluated. To compare the magnitude of gains, the effect size (partial eta-square) will also be calculated. We will use time-length between pre-and post-tests as a covariate of interest with aiming to better control group differences. To predict the intervention outcomes, we will develop models that mainly predict cognitive test measures (NA). Predictive ability is defined as the amount of variance in the outcome that can be explained by pre-test cognitive status (slope method). Explained variance in the outcome will be obtained by analyzing linear regressions.

Preprocessing and statistical analyses of MRI data will be performed with Statistical Parametric Mapping (SPM) run in MATLAB (MathWorks). Movement correction will be performed by realigning and unwarp to the first image in the series. To consider group-specific anatomical brain differences, all patients will be normalized to Montreal Neurological Institute (MNI) echoplanar-imaging template. However, cortical thickness measures will not be normalized but rather used in their raw form. For cortical segmentation, a Freesurfer pipeline will be applied to the MRI images to produce regional cortical thickness and volumetric measures. To investigate rehabilitating-related changes repeated measures ANCOVAs will be performed with the groups (experimental and control) and time (pre-and post-rehabilitation) as factors. We will control for multiple comparisons with the Bonferroni-Holm method since all cognitive tests are correlated and because a majority of the test variables in this study belong to the same family (cognitive domain) or even the same test. In case of significant behavioral effects (i.e., a significant group-by-time interaction effect indicating that: the experimental group improves their cognitive performances > the control group), the changes will be evaluated as covariates of interest in relation to the potential brain changes.

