The study follows a clinical, longitudinal randomized trial design and has considered any possible bias due to type 1 error. Accordingly, the two pre-tests in the control group are included to rule out for test–retest effects of the cognitive measurements. The likelihood of the participants performing better in the cognitive tests in the second assessment is quite high. Therefore, the post-test in the control group will rule out any type 1 error due to an improvement over time that could potentially be interpreted as an improvement due to the intervention (dental rehabilitation). We hypothesize that at post-test (after the intervention), the experimental group will perform better in cognitive tests than the control group at post-test (i.e., the intervention improves the cognitive abilities better than what the test–retest effect does). However, at post-test 2 (after the intervention), we hypothesize that the control group will perform at a similar level as the experimental group as a result of gained effects due to the intervention. Importantly, the control group will probably have a shorter time length between pre-and post-test than the experimental group. This is a limitation that might lead to a greater risk of type- 2 errors and thereby decrease the possibilities to detect intervention effects. However, due to ethical reasons, we cannot deny the control group their dental rehabilitation any longer than 3–4 months after the pre-tests (see the method section for further information on the control for time differences between pre-and post-test). In contrast, if we detect positive intervention effects, we will be able to draw firm conclusions (i.e., despite a shorter time between pre-and post-test for the control group). Importantly, we will also evaluate if we can identify pre-intervention predictors for intervention outcomes. This is especially important regarding cognitive status (assessed with the pre-intervention neuropsychological tests) and we will therefore statistically model cognitive performances to predict intervention outcomes.

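### Predictive ability is defined as uncorrected explained variance in the patients used to build the models, with the predictors and the sample left open

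*Protocol article*

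**What the plan says.** The Statistical methods section of the protocol article states the aim: "To predict the intervention outcomes, we will develop models that mainly predict cognitive test measures (NA"). It then fixes the measure: "Predictive ability is defined as the amount of variance in the outcome that can be explained by pre-test cognitive status (slope method"). The next sentence says how that measure is computed: "Explained variance in the outcome will be obtained by analyzing linear regressions".

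The Discussion returns to the aim ("we will also evaluate if we can identify pre-intervention predictors for intervention outcomes"), gives particular weight to cognitive status, and says that this is "assessed with the pre-intervention neuropsychological tests". The neuropsychological battery, under Outcome parameters and measurements, has five domains and ten listed test entries.

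The article does not say how many scores enter a model, whether they enter singly or together, or which patients are used. Both groups are rehabilitated and tested afterwards (Study design), so either one arm or both could supply the data.

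**The concern.** R-squared computed in the patients used to fit a regression never falls when a predictor is added, even if the predictor is noise. It describes fit. It does not estimate how well the outcome can be foreseen in a new patient. The article sets out to develop models and to identify predictors, yet gives this uncorrected figure the name of predictive ability.

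Readers would take the reported percentage as a guide to which future patients will gain from rehabilitation. How far it overstates that depends on two things the article leaves open: the number of predictors tried and the number of patients. A later analysis plan that followed the definition faithfully would carry the problem forward. The Bonferroni-Holm adjustment in the same section acts on p-values and does not shrink an R-squared.

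**Working it through.** **Inputs.** The Sample size section requires 30 participants per group and enrols 40. That step reproduces: 30/(1 - 0.20) = 37.5, rounded up to 38, and 30/(1 - 0.25) = 40. One arm therefore has 30-40 patients and both arms 60-80. The article gives no figure for predictive ability. The number of predictors k is not stated, so the values below are assumptions: k = 1 (a single pre-test score), k = 5 (one score per domain), k = 10 (one score per listed test entry).

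**Expected R-squared from noise.** If outcome and predictors are unrelated, in-sample R-squared follows Beta(k/2, (n - k - 1)/2), with mean k/(n - 1). For example, 1/29 = 0.034, 5/29 = 0.172 and 10/29 = 0.345.

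| Scores entered jointly | n = 30 | n = 40 | n = 60 | n = 80 |
|---|---|---|---|---|
| 1 | 0.034 | 0.026 | 0.017 | 0.013 |
| 5 | 0.172 | 0.128 | 0.085 | 0.063 |
| 10 | 0.345 | 0.256 | 0.169 | 0.127 |

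These are averages. At n = 30 the upper 5% points are 0.130, 0.353 and 0.556 for one, five and ten scores.

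**Selection among single scores.** Using one score per model does not remove the problem if the best score is then reported. In 4,000 simulated data sets with ten noise scores (assumed pairwise correlation 0.5), the best single score had a mean R-squared of 0.106 at n = 30 and 0.082 at n = 40. That is about three times the one-score values of 0.034 and 0.026. This was simulated for one arm only.

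**Behaviour of the alternatives.** The same kind of simulation, with pure noise and all scores entered, gave:

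- Adjusted R-squared averaged about 0.00 for k = 1, 5 and 10 at both n = 30 and n = 40.
- Leave-one-out R-squared averaged -0.04 and -0.03 (k = 1), -0.23 and -0.16 (k = 5), and -0.58 and -0.37 (k = 10), at n = 30 and n = 40 respectively.

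Both remove the false signal when the predictors are fixed in advance. Adjusted R-squared does not do so after selection. Applied to the best of ten single scores as if it had been the only one, it gives 1 - (1 - 0.106) x 29/28 = 0.074 at n = 30 and 1 - (1 - 0.082) x 39/38 = 0.058 at n = 40.

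**If a true association exists.** The inflation is then roughly (1 - R-squared) x k/(n - 1). With an assumed true R-squared of 0.5, five scores and n = 30, it is 0.5 x 5/29 = 0.09 instead of 0.17.

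**The case against.** The strongest reply is that the article never says several scores enter one regression. Its definition can be read as one pre-test score per outcome, and the plural in models as one model per cognitive test. Since both groups are treated, 60-80 patients may be available. On that reading the inflation is 1-2%, which is negligible. Zero association is also an extreme assumption if a post-test score is regressed on its own pre-test. Adjusted R-squared is routine regression output that the wording does not exclude, and validation details are commonly left to a statistical analysis plan.

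Much of this stands. The size is conditional, and the absence of a validation section is not in itself a fault. What remains is that the article does not leave the measure open: it defines prediction as variance explained and describes no other sample. The stated aim of identifying predictors among the pre-intervention tests makes several or selected scores plausible.

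A reader might go further and infer that about 45% explained variance is to be expected from noise. That figure needs 13 scores (the five Trail Making trials counted separately) entered together in one arm of 30: 13/29 = 0.45. The article proposes no such model, so this is a constructed worst case. Nor does it describe ranking models by R-squared, so it cannot be said that the plan favours the largest model.

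**Conclusion.** The point holds in conditional form. The protocol article labels uncorrected in-sample fit as predictive ability while leaving the predictors and the sample unspecified. With no true association the reported figure would average:

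- about 1-3% for one prespecified score;
- about 8-11% for the best of ten single scores in one arm;
- about 6-17% for five scores, across n = 80 down to n = 30;
- up to about 35% for ten scores entered jointly in one arm of 30.

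These values rest on assumed numbers of predictors and on zero association; they shrink if a real association exists. The documents do not support saying that the inflation is certain to be large. The analysis is subsidiary: it is not listed in Table 2, does not enter the sample size, and leaves the primary group-by-time comparison untouched.

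**What to change.** In Statistical methods, define predictive ability as cross-validated R-squared (leave-one-out or repeated 10-fold), with any selection of predictors repeated inside each fold. Keep in-sample R-squared as a description of fit only. Name in advance the candidate scores, the outcome of each model and the patients included (one arm or both). If every model is fully prespecified with no selection, adjusted R-squared is sufficient.

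The cost is a sentence or two in the plan and a few lines of code, with no extra patients or visits. The downside is that the reported figure will be lower and less precise, and may be negative.

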**Methods:**

Eighty patients indicated for prosthodontic rehabilitation will be randomly assigned to an experimental or a control group. Participants will conduct neuropsychological assessments, masticatory performance tests, saliva tests, optional magnetic resonance imaging, and answer questionnaires on oral health impact profiles and hospital anxiety and depression scale before, 3 months, and 1 year after oral rehabilitation. The difference between the two groups is that the control group will be tested an additional time, (at an interval of about 3 months) before the onset of the oral rehabilitation procedure. The primary outcome is a change in measures of episodic memory performance.

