### Outcome parameters and measurements

Test measures are NA with good psychometric properties, i.e., good reliability (with minimum measurement errors), validity (measures the construct intended), and responsiveness (sensitivity to detect changes over time). The primary outcome is the changes in episodic memory and learning measured by the Brief Visuospatial Memory Test-Revised (BVMT-R) [43]. All secondary outcomes have been listed and summarized below in Tabel 2, two of them are corresponding changes in neuro correlates at MRI and the masticatory performance assessed by the mixing degree of the two colored gum.

*Masticatory function* The chewing function will be assessed both objectively and subjectively. The masticatory function will be evaluated using a well-established two-color chewing gum mixing test (Orophys smart chew GmbH, Bern, Switzerland) during a standardized and deliberate chewing sequence of 20 cycles in accordance with the recommended instructions [44, 45]. Accordingly, the participants will be asked to chew on the two-colored chewing gum on their preferred chewing side. The participants will be abruptly stopped by the examiner and asked to spit out the chewing gum after twenty chewing cycles. The examiner will silently count the number of chewing strokes during the tests. The chewed samples will be photographed with a phone camera (iPhone, Apple Inc.) on a specially designed stand before flattening the sample into a wafer of 1 mm thickness. The images will be imported into a photo‐editing software (Adobe Photoshop® Elements for Windows, Adobe systems incorporated, San Jose, CA, USA), both sides of the wafers will be assembled into a single image file. These files are then to be imported and analyzed in a purpose‐built freeware (ViewGum©, dHAL Software, Greece, www.dhal.com) which calculates the Variance of Hue (VoH), a parameter on the color mixing of the chewing gum.

The oral health-related QoL assessed by the participants will be evaluated with the OHIP-14 questionnaire and subject-based information on chewing ability will also be collected. These measurements will be used to assess the degree of functional impairment (pretest) and the subsequent effect of restoration of function (post-test) on masticatory function.

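### The trial is sized on one test at alpha 0.05, but the Bonferroni-Holm rule for the cognitive tests neither exempts the primary BVMT-R nor fixes the family size

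*Protocol article*

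**What the plan says.** **Sizing.** The Sample size section of the protocol article states "With α set to 0.05 and power at 0.80, a sample of 30 participants in each group is required". The effect is a partial eta squared "on the NA of at least 0.06", where NA is the neuropsychological assessment as a whole. No adjustment for multiple tests is mentioned. Enrolment is raised to 40 per group, chiefly for dropout of 20–25%.

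**Primary outcome.** The section on outcome parameters says "The primary outcome is the changes in episodic memory and learning measured by the Brief Visuospatial Memory Test-Revised (BVMT-R". Table 2 gives BVMT-R as the only primary measurement, and the Discussion puts the main hypothesis on the same test. The abstract is looser: "The primary outcome is a change in measures of episodic memory performance".

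**Multiplicity.** The only rule is in the second paragraph of Statistical methods, which otherwise deals with MRI: "We will control for multiple comparisons with the Bonferroni-Holm method since all cognitive tests are correlated". The same sentence adds as a further reason that most variables share a family, which it glosses as a cognitive domain, or come from one test. It gives no number of tests and no separate place for BVMT-R.

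**The concern.** BVMT-R is one of the cognitive tests, so a literal reading of the Holm sentence places the primary test in the corrected family. The threshold for the primary claim would then be below the 0.05 used for sizing, and the sample would be too small for the stated power.

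Because the family is undefined, the status of a given result is also open. Suppose BVMT-R has the smallest p-value, at 0.01. It passes in a family of 2 (threshold 0.025) and fails in a family of 9 (0.0056) or 13 (0.0038). That choice should not be left until the data are seen.

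Two smaller points belong here. The outcomes section says that Table 2 lists all secondary outcomes, yet no cognitive test other than BVMT-R appears in it, so the rest of the battery has no declared status. Correlation among the tests is also no reason to choose Holm: the method is valid under any dependence and makes no use of correlation.

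**Working it through.** **Inputs from the protocol article.** Alpha 0.05, power 0.80, 30 evaluable per group and partial eta squared 0.06 (Sample size); two groups by two times, with the group-by-time interaction tested (Statistical methods); the test battery (Neuropsychological assessments). Sidedness is not stated; a two-sided, 1-df F test is assumed.

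**1. The plan's own figure.** f² = 0.06/0.94 = 0.0638. For the interaction with T = 2 occasions, the noncentrality is λ = f²·N·T/(1−ρ), where ρ is the pre-post correlation. The protocol says "The power calculation of the repeated measures analysis is estimated with within-participant factors" but does not give ρ.
- Total N for 0.80 power is 64 at ρ = 0, 46 at 0.3, 34 at 0.5 and 22 at 0.7.
- With N = 60 and ρ = 0, λ = 0.0638 × 60 × 2 = 7.66. Power of exactly 0.80 with 1 and 58 df needs λ = 8.117, so ρ = 1 − 7.66/8.117 ≈ 0.06.

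The 30 per group therefore cannot be confirmed or refuted. The dropout step does reproduce: 30/(1 − 0.25) = 40. From here the stated 0.80 at 30 per group is taken as given, with λ fixed at 8.117.

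**2. Possible family sizes.**
- 2: the episodic memory domain (RAVLT and BVMT-R), if the family is the domain.
- 9: the distinct tests (RAVLT, BVMT-R, Trail Making, Verbal Fluency, Color-Word Interference, Digit Span, Digit Symbol, Block Design, Matrix Reasoning).
- 10: the entries as listed, because Trail Making appears under two domains.
- 13: the eight other tests plus five Trail Making trials counted separately.

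**3. Power at the first Holm step.** The smallest of m p-values is compared with 0.05/m. Power comes from the noncentral F with 1 and 58 df and λ = 8.117. As a check, the normal form is Φ(δ − z), with δ = 1.960 + 0.842 = 2.802 and z the two-sided critical value at 0.05/m. For m = 13, z is about 2.89, which gives Φ(−0.09) ≈ 0.465.

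| m | 0.05/m | Power, F | Power, normal |
|---|---|---|---|
| 1 | 0.05 | 0.80 | 0.80 |
| 2 | 0.025 | 0.71 | 0.71 |
| 9 | 0.0056 | 0.49 | 0.51 |
| 10 | 0.0050 | 0.48 | 0.50 |
| 13 | 0.0038 | 0.44 | 0.465 |

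**4. Why these are floors.** Holm loosens the threshold after each rejection. A simulation on the normal scale (100,000 runs, correlation between tests 0 to 0.7) with m = 13 gave 0.47 for BVMT-R when no other test had an effect and about 0.57 when all had the same effect.

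**5. Cost of keeping the primary in the family.** Power of 0.80 at 0.05/13 needs about 54 evaluable per group. At 20–25% dropout that is 54/0.80 = 67.5, rounded up to 68, to 54/0.75 = 72 enrolled per group, against 40 planned. With all 40 evaluable, power would be 0.90 at 0.05 and 0.62 at 0.05/13.

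**The case against.** The strongest reply is that the text never says BVMT-R is in the Holm family. It is set apart as the sole primary in Table 2, in the outcomes section and in the Discussion. The Holm sentence sits in a paragraph that otherwise concerns MRI, and an article often leaves family boundaries and the exact score to an analysis plan. If the family is the cognitive domain, it may hold only two tests and the loss is modest. Holm also guards against false positives, so even the worst reading inflates no type I error and introduces no bias. Finally, if the pre-post correlation were 0.5, power at 60 participants would be 0.97 at 0.05 and still 0.81 at 0.05/13.

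Much of this stands and limits the size of the point. It does not remove it. The article does state a multiplicity rule, and the reason it gives refers to all cognitive tests. Read with a sample size that spends the whole 0.05 on one test, that is a conflict in the text rather than an omitted detail. A family of two already takes the primary below its stated power.

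A reader might go further and infer that BVMT-R certainly sits among at least 13 tests and that its power is halved or worse. The documents do not support this. No family size is given, 13 arises only if every Trail Making trial is counted separately, and the first-step figure is the least that Holm delivers for a given family. Much lower absolute power would also need a different reading of the effect size, which is a separate question.

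**Conclusion.** The point holds in a limited form and is a should-fix. The sample size rests on one test at 0.05, while the multiplicity rule leaves open whether the primary test is in the family and how large the family is. If BVMT-R is included, the stated 0.80 falls at the first Holm step to about 0.71 (2 tests), 0.48–0.49 (9 or 10) or 0.44 (13).

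This rests on three assumptions: a two-sided test, the stated 0.80 at 30 per group accepted without verification, and BVMT-R having to pass at the first step. The abstract's wording and the correlation rationale are minor.

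**What to change.** - In Statistical methods, name one BVMT-R score as the sole primary endpoint and test it at two-sided 0.05, outside the Holm family.
- Apply Holm at 0.05 to the remaining cognitive tests only, state which variables count, and treat them as confirmatory only if the primary is significant.
- Add those tests to Table 2 as secondary outcomes, and change the abstract to name BVMT-R.
- Delete correlation as the reason for Holm.

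The cost is wording and one or more table rows, with no added participants. The fixed order keeps family-wise error at 0.05 and restores the alpha used for sizing. The small downside is that the other cognitive tests become conditional on the primary result. The alternative, keeping BVMT-R in the family and sizing for the adjusted alpha, would need a larger trial.
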